### Data management

The data is collected on paper case report forms and then sent to the Derby Clinical Trials Unit where the data is entered onto an electronic database according the Derby Clinical Trials Unit standard operating protocol.

Confidentiality is maintained by the case report forms and the datasets used for analysis containing trial number and initials only.

The final trial dataset will be managed by the Derby Clinical Trials Unit and access to the data will be only with permission of the trial management group prior to publication. Following completion of the trial, the data will archived and the possibility of depositing the data in a public archive will be explored.

### Management of trial documentation

Each site is given, at their site initiation visit, a trial site file with all the current trial documentation. Document updates, as they occur are sent to each site. In addition, there is an on-line document depository (Trello board) where all current documents are held and maintained and to which all sites have access to.

There is a project manager whose role includes ensuring that documentation is current and up to date with all relevant parties.

### Statistical methods

Statistical analysis will be performed for each of the three groups (anisometropic amblyopia, strabismic or mixed amblyopia, post strabismus surgery) separately. Intention to treat will be the primary analysis including all patients randomised regardless of the received treatment. The primary outcome of visual acuity change from baseline to 6 weeks will be analysed using analysis of covariance (ANCOVA) with baseline visual acuity, age and centre as the covariates for comparing the I-BiT Plus treatment vs the standard treatment.

We will examine the plausibility that primary outcome data is missing at random (MAR) and multiple imputation techniques will be used to handle missing values as appropriate. The estimated effect sizes and their 95% confidence intervals will be reported according to Consolidated Standards of Reporting Trials (CONSORT) guidelines [18]. The level of significance is defined at 0.05.

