**Methods/design:**

This is a randomised controlled trial involving three groups of 40 patients each, aged between 3.5 and 12 years, with a diagnosis of (1) anisometropic amblyopia, (2) mixed or strabismic amblyopia prior to strabismic surgery and (3) mixed or strabismic amblyopia who have just undergone strabismus surgery. They will be randomised in a 1:1 ratio between I-BiT and control and will receive treatment, at home over a 6-week period. Their visual acuity will be assessed independently at baseline, mid-treatment (week 3), at the end of treatment (week 6) and, for those receiving the active I-BiT treatment, 4 weeks after completing treatment (week 10).

The primary endpoint will be the change in visual acuity from baseline to the end of treatment. Secondary endpoints will be additional visual acuity measures, patient acceptability, compliance and the incidence of adverse events.

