The basic study design is the same for all three groups and is summarised in Fig. 1.

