### Outcomes

#### Primary outcome

There are two primary endpoints for the trial arms:Feasibility will be assessed by the number of hours of treatment deliveredThe primary clinical endpoint will be the change of visual acuity from baseline to week 6 post receipt of the I-BiT Plus or laptop between the two arms in each group

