### Sample size

This is a pilot study and, therefore, formal sample size estimations have not been performed.

Based on 20 treated patients per arm, the minimum importance difference of 0.1 logMAR in visual acuity between the I-BiT Plus arm and standard care arm can be observed at 5% significant level with 80% power if the standard deviation is 0.15 logMAR or less. We do not have an accurate estimate of the standard deviation and a known unknown is the compliance rate (both with the treatment and with the trial procedures). The standard deviation in visual acuity at 6 weeks will be estimated to inform sample size calculations for the future trial which will assess clinical effectiveness of the I-BiT™ system.

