## Discussion

This is a randomised controlled trial for the revised I-BiT™ system. There is now a body of evidence that dichoptic stimulation is an effective treatment for amblyopia [9] and this trial builds on previous work [13, 14, 19]. We have used the lessons from the previous studies to redesign the I-BiT system with the following improvements:Home-based system. Simple to use and also safe. For example, it will switch itself off if it is left idle for 15 min. The current system is designed to be used without supervisionRange of games and videos (as opposed to one game and one video)Allow image off-setting for strabismic and mixed amblyopiaSimple psychophysical tests incorporatedMonitor activities undertaken and treatment time. It will not permit a treatment session to be longer than 1 h or more than 2 h in 1 dayWe also included a face verification system to help ensure that the person using the system is the intended participant

The major aim of this trial is as a feasibility study to see if all these features function as designed and at the same time get some indication of efficiency. The intention is to get sufficient information to allow a definitive study to be designed.

It should be noted that this approach is not without its problems. A major cause of treatment failure with patching is poor compliance [7, 20] but videogames must be engaging and can have their own compliance issues. In the PEDIG study, only 22% of participants complied with more than 75% of the prescribed treatment. The revised I-BiT has programmed up eight games in an attempt to ensure a reasonable choice and includes around 40 h of videos which are particularly targeted to the 3.5–6 years age range where they may be less inclined to the gaming options.

It is the issue of compliance that undermines any power calculation. We are just powered to detect a clinically significant difference but this is assuming good compliance. So it is likely that we will end up under powered, but we will have a measure of compliance which can be used for future calculations.

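### The primary acuity analysis is fixed as three separate 40-child ANCOVAs, each with about 54% power at the protocol's own figures; a supportive joint model should be added

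*Protocol article*

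**What the plan says.** The Statistical methods section of the protocol article sets the structure: "Statistical analysis will be performed for each of the three groups (anisometropic amblyopia, strabismic or mixed amblyopia, post strabismus surgery) separately". The primary acuity outcome is to be analysed by "analysis of covariance (ANCOVA) with baseline visual acuity, age and centre as the covariates". The Primary outcome section agrees, defining the clinical endpoint as a comparison "between the two arms in each group". The abstract plans "three groups of 40 patients each", "randomised in a 1:1 ratio between I-BiT and control", so 20 v 20 in each group and 60 v 60 in all.

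Under Trial design the article says "The basic study design is the same for all three groups", and in the same section it describes the groups as distinct, non-overlapping populations. The Sample size section claims 80% power with 20 per arm for 0.1 logMAR if the SD is at most 0.15, and adds: "The standard deviation in visual acuity at 6 weeks will be estimated to inform sample size calculations for the future trial". The Discussion concedes, on grounds of compliance: "So it is likely that we will end up under powered". No overall treatment effect, treatment-by-group comparison or pooled SD is described.

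**The concern.** The study wants an indication of efficacy and enough information to design a definitive trial. Its only planned efficacy comparisons are three small ones, each yielding an interval almost as wide on either side as the difference sought. If the device worked equally well in all three groups, the likeliest outcome would be a mixed set of significant and non-significant results. That could be taken for a difference between amblyopia types when it is only sampling variation. Separate analyses contain no direct comparison that would guard against this reading. If the children were combined only after the results were known, the combined estimate would carry little weight.

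**Working it through.** **Inputs.** From Sample size: 20 per arm, difference 0.1 logMAR, SD 0.15, 5% level, 80% power. From the abstract: three groups of 40, allocated 1:1. From Trial settings: four centres, hence three centre contrasts. Assumptions: a two-sided test (the article does not state sidedness but reports 95% intervals), 0.15 taken as the residual SD, and no dropout unless stated.

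**1. The stated 80%.** SE = SD × √(2/n) = 0.15 × √(2/20) = 0.0474. Difference/SE = 0.1/0.0474 = 2.108.
- Normal approximation: Φ(2.108 − 1.960) = 56%. Noncentral t on 38 df: 54%.
- One-sided: 68% (66% by t).
- n per arm for two-sided 80%: 2 × (0.15 × 2.802/0.1)² = 35.3, so 36. With 20 per arm the SD must be at most 0.1/(2.802 × √0.1) = 0.113.
- If 0.15 were an SD before covariate adjustment, a correlation of √(1 − (0.113/0.15)²), about 0.66, would be needed to reach 80%. The article states none.

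The 80% does not reproduce for the two-arm comparison.

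**2. One group.** Residual df = 40 − (intercept 1 + treatment 1 + baseline 1 + age 1 + centre 3) = 33. Half-width = 2.03 × 0.0474 = 0.096 to 0.097. Power is 53% on 33 df and 54% on 38 df. With a true effect of 0.1 in every group, all three tests are significant with probability 0.535³ = 15%. At most one is significant with probability 0.465³ + 3 × 0.535 × 0.465² = 45%.

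**3. Joint model, common effect.** Residual df = 120 − (intercept 1 + treatment 1 + group 2 + interaction 2 + baseline 1 + age 1 + centre 3) = 109. SE = 0.15 × √(2/60) = 0.0274; ratio 3.65. Power 95%; half-width 1.98 × 0.0274 = 0.054.

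**4. Sensitivity to the assumptions.**

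| Situation | One group | Joint |
|---|---|---|
| SD 0.10, common effect | 87% | >99% |
| SD 0.15, common effect | 53–54% | 95% |
| SD 0.20, common effect | 34% | 77% |
| SD 0.15, assumed 20% dropout (normal approximation) | 47% | 90% |
| SD 0.15, effect 0.1 in two groups, none in the third | n/a | about 68% |
| SD 0.15, effect 0.1 in one group only | n/a | about 23% |

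In the last two rows the average effect is 0.2/3 = 0.067 and 0.1/3 = 0.033, giving ratios to the SE of 2.43 and 1.22.

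**5. Interaction.** In either of those two cases the noncentrality is Σ(effect − mean)²/(0.15² × 2/20) = 0.00667/0.00225 = 2.96, and the 2-df F test has about 31% power. The difference between two group effects has SE √(2 × 0.00225) = 0.067 and half-width 1.98 × 0.067 = 0.133 logMAR.

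**6. SD for the next trial.** Limits are SD × √(df/χ²) at an estimate of 0.15.
- 33 df: 0.15 × √(33/50.73) = 0.121 to 0.15 × √(33/19.05) = 0.197.
- 109 df: 0.15 × √(109/139.78) = 0.132 to 0.15 × √(109/82.00) = 0.173.
- Put into 2 × (SD × 2.802/0.1)², these give about 23 to 61 per arm and 28 to 47 per arm.

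**The case against.** The best case for the plan is that separation is deliberate and coherent. The objectives pose the question in three scenarios, and endpoint and analysis both follow that. The groups do differ:
- Image off-setting is meant for strabismic or mixed amblyopia.
- Table 1 requires refractive adaptation in Group 1 but only if indicated in the others, so the control course may differ.
- Previous patching is barred in Group 1 and allowed elsewhere, and Group 3 starts soon after surgery.

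A common effect therefore cannot be presumed, and the interaction test is too weak to establish one. All of this stands. It rules out replacing the group analyses, but not adding a supportive model beside them.

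A second objection is that a supplementary model could sit in an analysis plan that is not shown. That is possible. But the article does not leave the structure open: it says the analysis is done separately. The point is about that choice, not about missing detail.

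Third, this is a feasibility study that reports intervals and warns of low power. That limits the consequences, but the article still sets a 0.05 significance level and makes acuity a primary endpoint.

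Some stronger readings are tempting but not supported. A reader might infer that the trial forfeits a pooled SD. Sample size does not say whether the SD is per group or pooled, and residual variances from three separate fits could be combined. A reader might also infer that every efficacy analysis is an ANCOVA, but the method is named only for the primary outcome. Nor are 120 children already in hand: that is the planned number, and Trial status reports 34 recruited in April 2018.

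**Conclusion.** The point holds as a recommended addition, not as an error in choosing group-specific analyses. The protocol fixes three comparisons with about 54% power each at its own SD and difference, and plans neither an overall estimate nor a direct comparison between groups. The stated 80% is wrong for 20 v 20 at SD 0.15.

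It would go too far to say that the full sample guarantees a well-powered answer. The 95% figure rests on a similar effect in all three groups, an SD near 0.15, a two-sided 5% test and the planned 60 v 60. Under a common effect, 80% power is kept up to an SD of about 0.195. Under unequal effects the gain shrinks or disappears, and a non-significant interaction would not show that the groups respond alike. What holds more generally is the narrower interval for the average effect, an explicit interval for between-group differences and, if the residual variances are similar, a tighter SD for planning.

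**What to change.** Keep the three group analyses as the primary result. Add to Statistical methods one prespecified supportive ANCOVA on all randomised children, with treatment, group, treatment-by-group, baseline acuity, age and centre. Report from it:
- the overall effect with its 95% CI, labelled supportive;
- the treatment-by-group contrasts with their CIs, without reading non-significance as evidence of homogeneity;
- the pooled residual SD beside the three group-specific SDs.

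Correct the Sample size statement as well: about 54% power at SD 0.15 with 20 per arm, or 80% only if the SD is about 0.11.

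The cost is a few lines of text and one further model, with no new children, visits or data. The drawback is that the overall effect averages over distinct populations with some differences in device set-up, control course and prior treatment, and that the model assumes common covariate slopes and residual variance. That is why it must remain supportive.

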### Eligibility criteria

These are summarised in Table 1.

**Table 1 Tab1:** Table of inclusion and exclusion criteria for the three groups in the clinical trial

Group 1	Group 2	Group 3
Anisometropic amblyopia	Strabismic or mixed amblyopia	Post-strabismus surgery
Inclusion criteria		
3.5^5^–12^4^ years	3.5^5^–12^4^ years	3.5^5^–12^4^
Vision in amblyopic eye between 0.3 and 1.3 logMAR with an intraocular difference of 0.2 logMAR or more	Vision in amblyopic eye between 0.3 and 1.3 logMAR with an intraocular difference of 0.2 logMAR or more	Vision in amblyopic eye between 0.3 and 1.3 logMAR with an intraocular difference of 0.2 logMAR or more
May have a manifest squint of less than or equal to 10 prism dioptres	Manifest squint must be greater than 10 prism dioptres	Residual squint following surgery (no more than 4 weeks prior) of any size
Undergone refractive adaptation^1^	Undergone refractive adaptation (if indicated)^1,2^	Undergone refractive adaptation (if indicated) ^1,2^
No previous patching or penalisation	Previous patching or penalisation acceptable	Previous patching or penalisation acceptable
No previous strabismus surgery	No previous strabismus surgery	Treatment to start within 4 weeks of strabismus surgery but no previous strabismus surgery
Can use I-BiT Plus	Can use I-BiT Plus	Can use I-BiT Plus
Exclusion criteria		
Deprivational amblyopia		
Presence of manifest nystagmus		
Other ocular or neurological disease affecting the visual system^3^		
Parent, guardian or child not prepared to give consent		

^1^Refractive adaptation is wearing refractive correction for a minimum of 12 weeks

^2^Refractive adaptation is indicated if there is a significant refractive error

^3^These include Down’s syndrome, developmental delay, craniofacial syndrome, foetal alcohol syndrome and cerebral palsy among other conditions

^4^The upper limit of the age range is 1 day before their 13th birthday

^5^The lower limit of the age range is 182 days after their third birthday

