### Randomisation and codebreaking

Patients will be assigned sequentially, as each one consents to the clinical investigation, into the I-BiT Plus or control arms using the Simon and Pocock minimisation method (with an 80% chance of attempting to balance) in order to achieve a 1:1 ratio. The minimisation will be stratified by the recruitment centre, age (3.5 – < 6, 6 – < 9 and 9–12 years as the treatment response – visual acuity – is strongly age dependant over this age range for conventional treatment) and history of previous treatment (Yes/No).

The randomisation sequence was generated by the Derby Trials Unit.

The treatment allocation will be done using a web-based randomisation system and undertaken by the research orthoptist at the baseline visit.

It is not possible to mask the intervention and so there is no requirement for code breaking.

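### The primary ANCOVA omits previous treatment, one of the three minimisation factors, so analysis and allocation do not match in Groups 2 and 3; any efficiency loss depends on how prognostic the factor is.

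*Protocol article*

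**What the plan says.** The Randomisation and codebreaking section of the protocol article describes minimisation "with an 80% chance of attempting to balance", "in order to achieve a 1:1 ratio". The balancing factors are recruitment centre, age in three bands, and "history of previous treatment (Yes/No". Amblyopia group is not listed among them.

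The Statistical methods section specifies the primary analysis as an ANCOVA of visual acuity change from baseline to 6 weeks, "with baseline visual acuity, age and centre as the covariates". It also states that "Statistical analysis will be performed for each of the three groups", separately.

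Table 1, under Eligibility criteria, requires "No previous patching or penalisation" in Group 1. For Groups 2 and 3 it reads "Previous patching or penalisation acceptable".

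**The concern.** When allocation is balanced on a factor that predicts outcome, the arms end up more alike on that factor than simple randomisation would make them. An analysis that ignores the factor still counts its variance as noise. The reported standard error then exceeds the real sampling variability of the treatment estimate, so confidence intervals are too wide and the test rejects too rarely. The model here carries two of the three balancing factors and drops the third.

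This is not a detail left for an analysis plan, because the protocol gives a definite covariate list that disagrees with its own allocation scheme. Precision is what is at stake. Each group has about 40 children, and the Discussion already expects the trial to end up underpowered.

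**Working it through.** **1. Factors side by side.**

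| Factor | Minimised on | In primary ANCOVA |
|---|---|---|
| Centre | yes | yes |
| Age | yes (bands) | yes |
| Previous treatment | yes | no |
| Baseline visual acuity | no | yes |

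Each group is analysed separately. Table 1 lets previous patching or penalisation vary in Groups 2 and 3 and bars it in Group 1.

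**2. The plan's own power figure.** The Sample size section, "Based on 20 treated patients per arm", claims 80% power for 0.1 logMAR at SD 0.15 and a 5% level. For two independent arms, two-sided (sidedness is not stated, but 95% intervals are to be reported):

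- SE = 0.15 × √(2/20) = 0.0474
- power = Φ(0.1/0.0474 − 1.96) = Φ(0.148) = 55.9% (53.8% by noncentral t)

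The 80% is not reproduced. That is a separate matter on which this point does not depend, but it sets the starting level for the comparisons below.

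**3. Formula for the omitted factor.** Let R² be the share of residual variance that previous treatment explains after baseline acuity, age and centre. The document gives no value, so 0 to 0.20 is an assumption. The SE without the factor, relative to the SE with it, is 1/√(1 − R²). Power with the factor uses SD 0.15 × √(1 − R²).

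| R² | SE ratio | Power with factor (normal approximation) |
|---|---|---|
| 0 | 1.000 | 55.9% |
| 0.05 | 1.026 | 58.0% |
| 0.10 | 1.054 | 60.3% |
| 0.20 | 1.118 | 65.4% |

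**4. Simulation of the actual scheme.** Pocock–Simon minimisation with probability 0.80, run within a group of 40. It used four centres, three age bands, SD 0.15, and half the children previously treated (assumed). ANCOVA was then fitted without and with the factor. Power is for 0.1 logMAR.

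| R² | Type I without | Type I with | Power without | Power with | Gain |
|---|---|---|---|---|---|
| 0 | 4.8% | 4.9% | 50.0% | 49.6% | −0.4 |
| 0.05 | 4.5% | 5.1% | 50.6% | 52.3% | 1.7 |
| 0.10 | 4.1% | 4.9% | 50.4% | 54.0% | 3.6 |
| 0.20 | 3.5% | 5.1% | 51.0% | 60.0% | 9.0 |

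At R² = 0.20 under no effect, the mean model SE without the factor was 0.0490 against an empirical SD of 0.0456. This confirms the direction.

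**5. If one minimisation runs across all three groups.** Balance within a group is then looser. At R² = 0.20, type I error without the factor was 4.5% instead of 3.5%, so the conservatism largely disappears. The precision available from adjustment remains: power was 48.0% without the factor and 55.7% with it. At R² = 0, including the factor cost 0.9 points (49.5% against 48.6%).

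**6. What the assumed R² implies.** If a proportion p was previously treated, R² corresponds to a difference in 6-week change between treated and untreated children of SD × √(R²/(p(1 − p))).

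- p = 0.5, R² = 0.05: 0.15 × √(0.05/0.25) = 0.067 logMAR
- p = 0.5, R² = 0.20: 0.15 × √(0.20/0.25) = 0.134 logMAR
- p = 0.9, R² = 0.05: 0.15 × √(0.05/0.09) = 0.112 logMAR
- p = 0.9, R² = 0.20: 0.15 × √(0.20/0.09) = 0.224 logMAR

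**7. Uneven splits.** A separate simulation (2,500 runs per setting, SD 0.15, effect 0.1, minimisation within group) fixed that difference at 0.07 logMAR. Power without and with the factor was 46.5% and 49.1% at 50% treated, 47.6% and 48.1% at 80%, and 49.2% and 49.3% at 90%. With a difference of 0.03 there was no gain at any split. Only the within-pair differences should be read, since each rate carries a Monte Carlo error of about √(0.5 × 0.5/2500) = 1.0 point.

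**The case against.** The strongest reply is that the loss is conditional and may be negligible.

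- **Prognostic value.** A reader might infer that previous treatment was made a balancing factor because response is expected to depend on it, and hence that the standard errors are too wide as a matter of fact. The protocol does not support this. The randomisation section gives a prognostic reason for age only and none for previous treatment. This objection stands, so the consequence has to be stated as conditional.
- **Size.** The top of the assumed range needs a 0.134 logMAR gap between previously treated and untreated children. That is larger than the 0.1 minimum important difference, and nearly twice the 0.07 improvement that the Background reports for all arms of the earlier randomised trial. The Discussion says most strabismic amblyopia presents before 3.5 years, so many children in Groups 2 and 3 may already have been treated, although no proportion is given. This also stands: gains near 9 points are an upper end.
- **Type I error.** The closed form 2 × (1 − Φ(1.96/√(1 − R²))) gives 0.044 at R² = 0.05 and 0.028 at R² = 0.20, which might suggest a markedly conservative test. It assumes perfect balance within each analysed group. Minimisation with 80% probability, and without amblyopia group as a listed factor, does not guarantee that. The simulated figures are the ones to use.
- **Purpose.** This is a feasibility study without a formal sample size, and the omission errs on the safe side. That limits the seriousness of the point. It does not explain why one balancing factor was left out, and the trial is meant to inform a definitive study.

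**Conclusion.** The mismatch is in the text and is unexplained: three factors are balanced and two are adjusted for. It concerns Groups 2 and 3. Group 1 is expected to be unaffected, because patching and penalisation are barred there. This is an expectation only, since the randomisation section does not define previous treatment and the Background calls refractive correction the first-line treatment.

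If previous treatment is prognostic after baseline acuity, age and centre, the intervals are somewhat too wide and the test mildly conservative. For R² from 0 to 0.20 with a 50:50 split and minimisation within group, type I error without the factor runs from about 5% to 3.5%. Adjustment gains from about zero to 9 points of power, and less with a lopsided split. These ranges rest on assumed values of R² and of the proportion treated.

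A reader should not conclude that the planned analysis is biased or that it inflates false positives, since neither follows. The change is worth making because it aligns analysis with allocation at almost no cost, not because a large loss has been shown.

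**What to change.** In Statistical methods, add previous treatment (yes or no, as recorded for minimisation) to the ANCOVA covariates for Groups 2 and 3, and state that the term drops out in any group where it does not vary, as expected in Group 1. If the sponsor prefers to leave it out, the reason should be given.

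The cost is one degree of freedom per model and no new data collection. If the factor turns out not to be prognostic, the simulated loss is under one point of power. The change should be made before outcome data are compared by arm.
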